### NKF- NUS Hemodialysis Self management Intervention

The NKF NUS hemodialysis self management program is based on the UCL diabetes self management program [27,56] but adapted to meet the needs of the target hemodialysis population in the local context. It emphasises patients' central role and responsibility in managing their illness. The program offers the potential for people to learn about their condition and treatment in a psychologically motivating and confidence enhancing structure - emphasis is on empowering patients to make choices and lifestyle changes in line with treatment recommendations through the use of problem solving, goal setting and feedback.

The NKF-NUS hemodialysis self management program has been developed after widespread consultation with patients and health care professionals using focus groups and in depths interviews.

The group based intervention consists of three main sessions held every two weeks and one booster session (a total of four 90 minute long sessions each with a 15 minute refreshment break halfway through). Sessions are facilitated by two health care professionals with experience of working with dialysis patients (medical social worker, renal nurse, renal dietician and/or psychologist). This has been planned to ensure assimilation of the self management program into existing renal services. Table 1 summarises program content.

**Table 1 T1:** Summary of Content of the NKF-NUS self management program

Session	Topic	Content
1	Fluid intake	General introduction to program; expectations;
		Introduction to fluid regulation; barriers to fluid regulation; problem solving; goal setting on fluid intake
2	Diet	Feedback on progress
		Review and revise goals from session 1.
		Introduction to Healthy eating in the context of ESRD; Difficulties related to diet; problem solving, goal setting on diet
		+ BROCHURE 'Healthy eating for people of dialysis'
3	Medication *	Feedback on progress
		Review and revise goals on diet and fluid
		Introduce to medication for patients on dialysis; barriers to taking medication; problem solving; goal setting on medication.
		Discussing potential/preventing Goal Lapses
		Dealing with Goal Lapses
		+ BROCHURE 'process of problem solving'
	* Exercise [only if group has no issues with medication]	Introduce exercise for patients on dialysis; Barriers to exercise; problem solving' goal setting on exercise
	Telephone follow up	Feedback on progress
		Review and revise goals
4	Booster session	Group activity to revisit program topics; revisiting expectations
		Feedback on progress; Review and revise goals
		Use problem solving to overcome problems
		Lapses, relapses and maintenance of behaviour
		Maintaining changes over time
		Goal Setting
		+ BROCHURE 'process of problem solving'

Sessions in the program are based on psychological theories and techniques that have previously been employed to enhance and maintain health behavior change [57,58]. Intervention components will include problem solving, overcoming barriers, challenging beliefs, conducting brainstorming sessions, goal setting, and reinforcement and group processes. These self-management techniques are taught by means of skills mastery through biweekly action planning and feedback on progress, modeling of self-management behaviours and problem-solving strategies, and social persuasion through group support and guidance for individual self-management efforts. Targeted behaviours will include fluid control, diet, medication and/or exercise.

Patients are required to implement the coping-strategies taught from each session between sessions. Each session will be broadly structured to consist of a brief introduction to the theme, elicitation of patients' views on the topic, addressing of misconceptions, group discussion of possible coping strategies, identification of barriers to change, training in specific management strategies, drawing up of individual goals to be achieved, formulating actions plans to achieve these goals and reviewing previously set goals.

Patients will be contacted by telephone 2 months post intervention by one of the group facilitators (either psychologist, nurse or social worker) to assess the progress they are making with their goals. This will provide an ongoing interaction between the healthcare professional and the patients and will thereby represent an additional support system. A booster session will also be provided for participants 3 months after completion of the initial intervention. This will allow patients the opportunity to review their progress, address maintenance of behaviours over time and explore reasons for success and failure. The booster session will also remind patients of the principles of self management, problem-solving, action planning and will provide revision of important behavioural areas and reset goals. This booster session will be led by the same group facilitators.

### Missed sessions

If participants do not attend a session they will be sent any missed materials and, where possible, the session will be held over the telephone by one of the facilitators. Participants receiving the intervention will continue to have access to services available as part of their usual health care

### Delivery of intervention

To implement the proposed self management intervention, a number of healthcare professionals including renal nurses, renal dieticians and medical social workers already working extensively with the renal patient population in the National Kidney Foundation will be trained in the self management principles required for delivery of the intervention. This will allow the facilitators to run group sessions using the self management skills of problem solving, decision making, resource utilization, formation of patient/heath care provider partnerships and taking action. This program will be formulized in a manual with an accompanying training course, thereby facilitating rollout across the health/renal services and enabling any benefits accruing in the study to be broadly implemented.

### Quality assurance and Fidelity of Intervention

Fidelity rating for the intervention will first be evaluated in the preliminary phase of supervised pilot sessions; this consists of 4 pilot groups which will be scheduled to complete prior to the main trial to enable further training for facilitators. Intervention consistency and quality will also be assessed throughout the trial. A random subset of the intervention sessions will be observed. The delivery of the intervention will be evaluated using a criterion based checklist for each session. The criteria will include assessment of intervention techniques used (e.g. rapport building, problem solving, reinforcement) as well as a checklist against the content objectives for each session (e.g. whether facilitators kept to their roles and how well they explained/guided participants on setting goals). Summary notes from those facilitating the sessions will also be collated for further analysis. A sub-sample of the intervention facilitators will be asked to participate in a brief semi-structured interview to understand their experience of the intervention and their perceived competence in delivering and facilitating the session. Finally structured notes (e.g. how long each session, where it was delivered, etc.) will be collected to ascertain the effect of various setting and contextual factors.

A trial steering group will meet at regular intervals throughout the trial and advise on any issues that arise. The senior research team will provide feedback and support to the data collection and intervention facilitators' teams.

### Statistical Considerations

Outcomes will be analysed immediately after the intervention and then at 3 and 9 months

separately on an intention to treat basis. Analyses of covariance (ANCOVAs) will be performed for each outcome to examine changes within groups (Intervention vs. standard care control) comparing baseline to follow-up assessments. Covariates used will include baseline levels and other casemix differences between the groups (if any). The statistical significance criterion will be set at *P *< 0.05.

In addition to this intention-to-treat analysis we will also undertake a "per protocol" analysis on those individuals who attended all of the educational sessions in the intervention arm.

No formal subgroup analyses are planned. However exploratory analysis of the impact of patient level factors (e.g. age, gender, ethnicity and time on dialysis) on the effect of the intervention will be carried out.

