**Methods/Design:**

This is a multicentre parallel arm block randomized controlled trial (RCT) of a four session group self management intervention for hemodialysis patients delivered by health care professionals compared to standard care. A total of 176 consenting adults maintained on hemodialysis for a minimum of 6 months will be randomized to receive the self management intervention or standard care. Primary outcomes are biochemical markers of clinical status and adherence. Secondary outcomes include general health related quality of life, disease-specific quality of life, mood, self efficacy and self-reported adherence. Outcomes will be measured at baseline, immediately post-intervention and at 3 and 9 months post-intervention by an independent assessor and analysed on intention to treat principles with linear mixed-effects models across all time points. A qualitative component will examine which aspects of program participants found particularly useful and any barriers to change.

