### Sample calculation

Using serum phosphate levels as a physiological index of adherence to diet and medication) and Kidney disease specific QoL as primary outcomes, a total sample size of 126 and 128 respectively, were calculated. This was using 80% power (alpha = 0.05) to detect a significant absolute change of 1.5% in phosphate control and of 5 points (0.5 standard deviation) in the physical and mental component subscale scores in kidney disease QoL short form questionnaire [40]. Taking the larger number of 128 participants (64 in intervention and 64 in control group), a final total number of 154 participants (77 in each group) is needed to ensure at least an 80% final response rate is met (attrition/drop-out rate estimated at 20%). A target sample of 154 participants will be sought.

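### The main analysis is stated two ways (one mixed model over all visits, or a separate ANCOVA at each visit), neither is named primary, and covariates are chosen from observed imbalance

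*Protocol article*

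**What the plan says.** The Methods/Design part of the abstract says that outcomes, measured at baseline and three follow-ups, will be "analysed on intention to treat principles with linear mixed-effects models across all time points".

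Statistical Considerations says that the post-intervention, 3-month and 9-month outcomes will each be analysed "separately on an intention to treat basis". It continues: "Analyses of covariance (ANCOVAs) will be performed for each outcome to examine changes within groups (Intervention vs. standard care control) comparing baseline to follow-up" assessments. No mixed model appears there.

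On adjustment, the same section says "Covariates used will include baseline levels and other casemix differences between the groups (if any").

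Study Objectives sets the aim as an evaluation of the intervention against standard care, which is a comparison between arms.

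**The concern.** A joint model of all visits and a set of separate single-visit models are different analyses. They use different data for the 9-month estimate, handle the correlation between visits differently, and can give different results. Each is presented as the intention-to-treat analysis, and nothing makes one subordinate to the other. A later analysis plan or results paper could follow either and claim that it was specified in advance, so the choice can be made after the results are known.

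The covariate rule adds a second open choice. If the covariate set is settled only once the arms have been compared, the model depends on the data. It also selects variables because they are unbalanced, not because they predict the outcome.

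The phrase about change within groups adds a third problem. Read literally, the sentence that defines the effect names a contrast that does not answer the trial's question.

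**Working it through.** **1. The two statements side by side**

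| Feature | Abstract, Methods/Design | Statistical Considerations |
|---|---|---|
| Model | Linear mixed-effects | ANCOVA |
| Visits | All jointly | Each follow-up separately |
| Population label | Intention to treat | Intention to treat |
| Rank | None given | None given |

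Both cannot be the main analysis. Primary outcome measures lists weight gain, blood pressure, phosphate, calcium-phosphate product and potassium. Counting blood pressure once, that is 5 measures. The abstract implies 5 joint models; Statistical Considerations implies 5 × 3 = 15 separate ANCOVAs.

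**2. Covariates.** The rule fixes the baseline value and leaves the rest conditional on finding a difference between the arms. This is a stated rule, not a gap. The article already collects age (Measures) and comorbidity indices and dialysis history (Other Clinical Measures), so a fixed list is possible now.

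**3. The contrast.** The sentence speaks of change within groups but adds both arms in parentheses, and the next sentence adjusts for baseline. Baseline adjustment makes sense for a between-arm comparison, and Study Objectives asks for one. The wording is wrong; the intended analysis probably is not.

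**4. Plan's own figures.** Inputs from Sample calculation: 0.5 SD (5 points, SD 10), 80% power, alpha 0.05 (two-sided assumed).
- Normal formula: n per arm = 2(1.96 + 0.84)² × 10² / 5² = 62.8, so 63. The t-test version gives 63.8, so 64 per arm and 128 in total, as stated.
- The stated 154 matches 128 × 1.2 = 153.6. Dividing by 0.8 would give 160.

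**5. What would follow if the per-visit ANCOVA used only patients seen at that visit.** This is a supposition; the article does not say it.
- If 20% lacked the 9-month value: 154 × 0.2 = 30.8 patients missing, leaving 154 × 0.8 / 2 = 61.6 per arm.
- Power = Φ(0.5 / √(2/n) − 1.96), ignoring clustering. It is 87.3% at n = 77 and 79.2% at n = 61.6. Baseline adjustment multiplies the SD by √(1 − r²) and raises the 79.2% to 82.9%, 89.3% or 97.3% for assumed r = 0.3, 0.5 or 0.7. Power is not the main stake.
- Bias at 9 months, by simulation with no true effect. All settings are assumed: correlation 0.6 between visits, and loss at 9 months depending on the observed 3-month value.

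| Assumed drop-out | Loss | Observed-case ANCOVA | All-visit likelihood-type estimate |
|---|---|---|---|
| Unrelated to outcome | 18% | 0.00 SD | 0.00 SD |
| One arm only, log-odds 1 per SD | about 20% in that arm | about −0.04 SD | about 0.00 SD |
| Opposite directions by arm, log-odds 0.5 | 19% | −0.05 SD | 0.00 SD |
| Opposite directions by arm, log-odds 1 | 22% | −0.10 SD | 0.00 SD |

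- Scale: 0.04 / 0.5 = 8% of the design effect. With 61.6 per arm and r = 0.6, the standard error is √(2 × 0.64 / 61.6) = 0.144 SD, so 0.04 SD is 0.28 standard errors. Two-sided type I error rises from 5.0% to about 5.9%.
- Precision when loss is unrelated to outcome: empirical standard error 0.140 SD for ANCOVA and 0.137 SD for the all-visit estimate.

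**The case against.** A reader might infer that the ANCOVA version drops patients with missing visits and so is not the intention-to-treat analysis it claims to be. The article does not support that. It says intention to treat, is silent on missing data, and neither states a complete-case analysis nor rules out imputation. An article commonly leaves that to the full plan. Even without imputation, a patient would be lost only from the visit missed.

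Nor can about 31 lost patients be asserted for the primary outcomes. The 20% in Sample calculation is an allowance for attrition tied to a final response rate, whereas the primary outcomes come from chart reviews. A missed questionnaire does not by itself mean a missing laboratory value.

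The larger biases in the table need drop-out to run in opposite directions in the two arms, which nothing in the article suggests. The mixed model's advantage also has a limit: it holds when loss depends on earlier observed values, not for values that do not exist because the patient has died.

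The phrase about change within groups might be read as a plan to test each arm separately. The parenthesis and the baseline covariate argue against that. Finally, baseline-adjusted ANCOVA at each visit is a legitimate method, and naming either method once would remove the contradiction.

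All of this stands, and it limits the point. It does not answer the two conflicting statements or the covariate rule, both of which are in the text.

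**Conclusion.** The point holds as a contradiction and a badly fixed rule. The abstract and Statistical Considerations give different main analyses and rank neither, and the adjustment set is left to observed imbalance. Both must be settled before outcome data are examined by arm. The within-group phrase is an error of wording.

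The contradiction has no single numerical size. Its consequence is a free choice, for every outcome, between one joint model and three separate ones. Bias from missing visits is a possible consequence of the ANCOVA version and not a demonstrated error. It is about 0.04 SD under the one-arm drop-out assumption and nil if drop-out is unrelated to outcome. An analysis plan that is not shown may already have chosen, but the article as published supports either choice.

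**What to change.** 1. Name one primary analysis and make the abstract and Statistical Considerations agree. The mixed model is the natural choice: the abstract already promises it, it uses all follow-up visits, and it stays valid if drop-out depends on earlier observed values. Fit baseline value, centre, visit and treatment-by-visit as fixed effects.
2. Include the randomised shift-within-centre cluster as a random effect, not a fixed one. In the Randomization section's example, one set of dialysis days in a centre is intervention and the other is control, so a fixed shift term within centre would be confounded with treatment.
3. Label the per-visit ANCOVA as a sensitivity analysis.
4. Replace the reference to change within groups by the difference between groups.
5. Replace the imbalance-driven rule with a short prognostic list fixed in advance from data already collected, for example age, comorbidity index and time on dialysis.

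The cost is revised wording in the protocol or analysis plan and slightly more programming. No new data are needed.

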### Study Objectives

1. To implement a group based self management intervention for patients on hemodialysis

2. To undertake an evaluation of this self management intervention comparing it with "standard care". The primary aim is to determine the efficacy of the self management intervention on biochemical markers of clinical status and adherence. Secondary aims are to determine the effect impact on QoL, mood, self-efficacy and patient satisfaction.

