#### Primary outcome measures

Beginning at baseline (Time 1) and continuing into follow up (Time 2, Time 3, Time 4) regular chart reviews will be conducted to abstract clinical, laboratory, and pharmacological data including:

(1) Interdialytic weight gain: The amount of weight gained between the end of one dialysis session and the beginning of the next. This is a validated marker of adherence to fluid restriction/regulation.

(2) Blood pressure

(3) Serum phosphate and calcium × phosphate product indicating a patient's adherence to prescribed oral phosphate binder medications and dietary phosphate restriction.

(4) Serum potassium indicating adherence to dietary recommendations.

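### The per-protocol analysis selects on full attendance in the intervention arm only, so it loses the protection of randomisation and can lean toward benefit

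*Protocol article*

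**What the plan says.** Under Statistical Considerations, outcomes are analysed by ITT separately at each follow-up. The method is ANCOVA with baseline level and any casemix differences as covariates. The article then adds: "In addition to this intention-to-treat analysis we will also undertake" a per-protocol "analysis on those individuals who attended all of the educational sessions in the intervention arm". No restriction on controls is mentioned. The significance criterion of P < 0.05 is given once, with no statement that the per-protocol result is exploratory, although the analyses of patient-level factors are labelled so.

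Four other places bear on this:

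- **Outcomes.** Study Objectives sets the primary aim to "determine the efficacy of the self management intervention on biochemical markers of clinical status and adherence". Primary outcome measures describes phosphate and calcium × phosphate product as "indicating a patient's adherence to prescribed oral phosphate binder medications and dietary phosphate restriction", and gives weight gain and potassium similar roles.
- **Programme.** The intervention section counts four sessions, three main and one booster: "A booster session will also be provided for participants 3 months after completion of the initial intervention".
- **Missed sessions.** Absent patients are sent the materials and, "where possible, the session will be held over the telephone by one of the facilitators". Whether that counts as attending is not said.
- **Entry.** Participants requires willingness to attend every session. This is judged before allocation and so applies to both arms.

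**The concern.** The per-protocol set is defined by something that happens after randomisation and can be seen in one arm only. The Discussion offers controls the programme only once the trial has ended, so the natural reading is selected attenders against all controls. That reading is inferred, but no attendance-based restriction of controls is possible.

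The selection is unlikely to be neutral here. Sessions are at weekends and, by the Setting section, ask a good deal of patients. Those who complete all of them are plausibly the ones who also keep to fluid, diet and medication advice, which is what the primary markers measure. The Background attributes non-adherence to psychosocial rather than clinical or sociodemographic variables, so casemix adjustment may miss much of the difference. It also reports greater weight gain and higher phosphate in patients who skip dialysis. That is a different kind of attendance and acts directly on the markers, but it points the same way.

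At stake is a second set of P values, printed beside the ITT results, that does not estimate an effect of attending.

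**Working it through.** **Inputs from the article.** 64 evaluable patients per arm, 77 recruited per arm, 20% attrition, alpha 0.05 (taken as two-sided), baseline-adjusted ANCOVA. The 64 reproduces: a two-sample t-test for 0.5 SD at 80% power needs 63.8, so 64 per arm. With 20% loss from 77, 77 × 0.8 = 61.6, so 62 controls.

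**Inputs assumed (not in the article).** Full attenders are better than other patients by d = 0.3–0.5 SD at baseline and follow-up alike. A share a = 50%–70% attends everything. The baseline to follow-up correlation is ρ = 0.5. The true effect is zero. Shift clustering is ignored, and the per-protocol analysis is taken to use the same ANCOVA as ITT.

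**Formulas.** The attender mean exceeds the whole-arm mean by d − a·d, so:

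- unadjusted bias = d(1 − a), outcome SD 1
- baseline-adjusted bias ≈ d(1 − a)(1 − ρ), residual SD √(1 − ρ²) = √0.75 = 0.866
- standard error = SD × √(1/(62a) + 1/62), with rejection probability from the non-central t distribution

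**Worst corner (d = 0.5, a = 0.5; 31 attenders, 62 controls).** Unadjusted: 0.5 × 0.5 = 0.25 SD; standard error 0.220; ratio 1.14; rejection 20%. Adjusted: 0.25 × 0.5 = 0.125 SD; standard error 0.866 × 0.220 = 0.190; ratio 0.66; rejection 10%.

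| d | a | Bias, unadjusted | Rejection | Bias, adjusted | Rejection |
|---|---|---|---|---|---|
| 0.3 | 0.7 | 0.09 SD | 7% | 0.045 SD | 6% |
| 0.3 | 0.5 | 0.15 SD | 10% | 0.075 SD | 7% |
| 0.5 | 0.7 | 0.15 SD | 12% | 0.075 SD | 7% |
| 0.5 | 0.5 | 0.25 SD | 20% | 0.125 SD | 10% |

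At ρ = 0.7 the worst corner falls to 0.25 × 0.3 = 0.075 SD and about 8%.

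**Is one-sided selection the cause?** A separate simulation of the ANCOVA under no effect (64 per arm, 3,000 runs per setting) let latent adherence drive both attendance and outcome, again with ρ = 0.5.

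- Attenders against all controls, correlation 0.2–0.5: bias 0.06–0.21 SD and rejection 6%–19% at 50%–70% attendance; 0.02–0.05 SD and about 5%–7% at 90%.
- Correlation 0: no bias, rejection about 5%.
- ITT: bias about 0, rejection about 4%–7%.
- The same latent selection in both arms: rejection about 4%–6%.

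The 19% comes from a wider gap than the table allows. At correlation 0.5 and 50% attendance, attenders lie 0.399 SD above the arm mean, so d = 0.399/0.5 = 0.8 SD.

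**Timing.** Time 2 is immediately after the intervention, Time 3 is at 3 months, and the booster comes 3 months after the initial course. If the booster counts as an educational session, the Time 2 set depends on behaviour about 3 months after that assessment, and the Time 3 set on behaviour at about the same time. If only the three main sessions count, this does not arise. The article does not say which.

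**The case against.** The strongest reply is that this is a secondary analysis, plainly additional to ITT, and that the bias is conditional. That stands. A reader might infer that the analysis will show benefit whatever the truth. The article does not support that, because the bias needs attendance to predict outcome beyond baseline. It is small when nearly everyone attends, and the willingness criterion narrows the gap in both arms. Attendance also partly reflects distance and weekend logistics rather than adherence. But stated willingness is not attendance, and nothing suggests the remaining selection is neutral.

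The planned baseline adjustment also matters. Under the assumptions above it about halves the unadjusted figures, so those should not be quoted as the expected size. Nor should the bias be set against the planned 0.5 SD, which refers to the quality-of-life component scores and not to the biochemical markers.

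A reader might also infer that the analysis is meant to rescue a null ITT result. Nothing in the article says so.

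Finally, the details of which sessions count could properly sit in a fuller document. That is fair for the booster and telephone sessions. It does not answer the main point, because the one-sided selection is stated in the article itself.

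A complier-average analysis has its own weakness here. Patients below any attendance threshold may still get materials, telephone sessions and the 2-month call, so allocation may act on them too.

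**Conclusion.** The point holds in a limited form. As stated, the per-protocol comparison is not protected by randomisation and can be biased toward benefit with no true effect. Under the assumed attender gap, attendance share and baseline correlation, the planned ANCOVA gives about 0.05–0.13 SD of spurious benefit and a false-positive rate of about 6%–10% (0.09–0.25 SD and 7%–20% without adjustment). If attendance carries no information beyond baseline, the bias is zero. The booster problem is conditional on the booster counting as a session. The ITT analysis and its conclusion are untouched.

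**What to change.** Estimate the effect of attendance with a complier-average causal effect model that uses allocation as the instrument, retains all randomised patients and keeps the clustering by dialysis shift.

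- Define receipt on the three main sessions only, which are complete before Time 2.
- State whether a telephone make-up session counts.
- State the exclusion restriction as an assumption, since mailed materials and calls reach non-attenders. Add a sensitivity analysis, for example counting any session, in person or by telephone, as received.
- If the attender comparison is kept, report it as descriptive, without a P value and not as support for efficacy.

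The cost is some wording, one additional model and a wider interval. With no access in controls, the estimate is roughly the ITT effect divided by the share receiving. If that share were 70% or 50%, the interval would be about 1/0.7 = 1.4 or 1/0.5 = 2 times as wide as the ITT interval.
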